#### Perceived self-efficacy for fatigue self-management scale (PSEFSM)

The PSEFSM is a valid 6-item instrument developed to measure self-efficacy in CRF management [30]. An 11-point scale (0–10, 10 = very certain) measures perceived ability to self-manage fatigue. Scores of the six items are averaged and final score ranges from 0 to 10 with 10 being highest perceived self-efficacy.

#### EuroQol 5 Dimension 5 Level Scale (EQ-5D-5L)

The EQ-5D-5L is a 5-item measure of health-related quality of life (HRQoL) [31]. One item is used to rate each dimension of mobility, self-care, usual activities, pain/discomfort and anxiety/depression on a Likert scale. Response options are as follows: no problems (0), slight problems (1), moderate problems (2), severe problems (3) and extreme problems (4). A final question asks the participant to rate their health from 0 (worst) to 100 (best) on a visual analogue scale. Scores for the five dimensions can be added to describe the patient’s health state with a possible range 0–20, with higher scores indicating worse HRQoL.

#### Perceived changes to personal, social and lifestyle factors

A study-devised questionnaire assesses perceived changes in personal, social and lifestyle factors related to fatigue that are targeted in the REFRESH program. These are sleep, mood, anxiety/worry, energy, exercise levels, social activity and engagement in hobbies. Response options for each item are follows: ‘Better’, ‘Same’ or ‘Worse’ (since starting the program). If participants select ‘Better’ on any given item, they are further prompted to record which stage of the booklet or program they believe the change/benefit for that domain was noticed.

### Data analysis

The target sample of 50 participants is based on available funding, resources (e.g. clinician time to deliver STEP 2) and study duration of 12 months. Whilst this sample size is in line with pilot and feasibility trials reported elsewhere [32], there is yet to be a clear consensus as to appropriate sample size for feasibility studies [33].

Analyses will include all available data and will be performed in R (reference index version 3.6.1 or higher) [34]. Descriptive statistics will be used to summarise demographic and clinical characteristics of all study participants. These will include counts and percentages for nominal and crude-scale ordinal (< 10 levels) valued variables and means and standard deviations or medians and interquartile ranges, as appropriate, for fine-scale (≥10 levels) ordinal and continuous valued variables.

The main implementation outcomes are acceptability, satisfaction, appropriateness and intervention feasibility of the stepped-care CBT intervention. These will be summarised using descriptive statistics. Recruitment data will be summarised using a rate and 95% CI using the Poisson distribution. Adherence and retention data will be summarised using a proportion and 95% CI; this will be estimated using the Wilson method.

Changes from baseline at follow-up assessments for fatigue (FACIT-F), self-efficacy (PSEFSM) and quality of life (Ed-5D-5L) will be analysed descriptively (means and standard deviations). This will be done separately for participants who undertake STEP 1 only and for those who participate in STEP 1 and STEP 2. Effect size estimates (i.e. standardised measures of change from baseline; in this case, mean change divided by the baseline standard deviation), as described by Kazis, Anderson and Meenen [35] will be used to characterise the size of observed differences.

Free text items from participant questionnaires will be summarised using content analysis, whereby the content of free responses will be coded and grouped, where applicable. Since the free text items mostly accompany pre-determined response options, it is not envisaged that all participants will respond to free-text items.

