#### Time 1 assessments (T1)

After 5 weeks, participants will complete a follow-up questionnaire. The T1 questionnaire includes fatigue, quality of life and self-efficacy questions (repeated T0 measures), in addition to feasibility and satisfaction measures (see “study measures” below).

#### Eligibility for STEP 2

Eligibility for STEP 2 is based on a participant’s change in fatigue scores following STEP 1. Fatigue will be measured using the Functional Assessment of Chronic Illness Therapy—fatigue subscale (FACIT-F) scores [22]. Participants with a T1 FACIT-F score greater than 34 or at least 10 points greater than T0 will be encouraged to continue their strategies without further CBT intervention. Participants with a FACIT-F score on the T1 questionnaire below 34 (severe) or less than 10 points greater than T0 will be considered for STEP 2 in conjunction with a psychologist’s clinical judgement of further support needs.

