#### Time 2 assessments (T2)

At 10 weeks post T0 (for STEP 1 only completers) or at the completion of STEP 2, all participants will complete a final T2 questionnaire. Completion of the T2 questionnaire marks the end of participation in the REFRESH study.

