## Discussion

The REFRESH study is the first to explore the feasibility of a stepped-care approach to persistent CRF amongst individuals who have completed cancer treatment or are on long term maintenance treatment. With a pragmatic study design, it aligns with common clinical practice. This may facilitate translation of the stepped-care intervention into practice. Although not powered to determine effectiveness, if at least half of the participants achieve a clinically meaningful improvement using supported self-management (STEP 1) alone, it will have the potential to reach many people suffering with CRF. Each person needing STEP 2 will require an additional 4 h of therapist time and some administrative time. This increases costs per participant and service capacity to deliver. Therefore, STEP 2 will be offered pragmatically in small group formats to manage demand and adhere to project timelines, as would occur in real world practice.

If feasible, a stepped-care approach could enable many survivors to access CBT for post-cancer fatigue.

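### Change is reported only from T0, so no planned figure covers the STEP 2 phase, and the T1-to-T2 FACIT-F rise that readers can obtain by subtraction is inflated because T1 selects people into STEP 2.

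*Protocol article*

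**What the plan says.** Under Data analysis, "Changes from baseline at follow-up assessments for fatigue (FACIT-F), self-efficacy (PSEFSM) and quality of life (Ed-5D-5L) will be analysed descriptively". The next sentence splits the summary: "This will be done separately for participants who undertake STEP 1 only and for those who participate in STEP 1 and STEP 2". Effect sizes are "standardised measures of change from baseline; in this case, mean change divided by the baseline standard deviation". Every planned change is therefore referenced to T0.

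T1, after 5 weeks, is the only planned repeat of the T0 measures before STEP 2. It also decides who is considered for STEP 2: "FACIT-F score on the T1 questionnaire below 34 (severe) or less than 10 points greater than T0 will be considered for STEP 2", together with the psychologist's judgement. The sentence before it sets the opposite route: "Participants with a T1 FACIT-F score greater than 34 or at least 10 points greater than T0 will be encouraged to continue their strategies". A separate contingency lets some participants be fast-tracked to STEP 2 early in STEP 1.

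T2 falls "At 10 weeks post T0 (for STEP 1 only completers) or at the completion of STEP 2". The study is single-arm. Its secondary aim, at the end of the Background, is whether taking part in the stepped-care intervention shows promise. The Discussion says of cost: "Each person needing STEP 2 will require an additional 4 h of therapist time".

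**The concern.** In the STEP 1 plus STEP 2 group, T0 to T2 combines STEP 1, any wait and STEP 2. Someone deciding whether to fund the therapist-led step will want to know what happened during it, and no planned figure says so.

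Readers are likely to build one. Because change is reported at the follow-up assessments, T0-T1 and T0-T2 would both appear for the STEP 2 group, and the difference between the means looks like the STEP 2 phase. But people are in that group because their T1 score was low or their T0-T1 gain was small. Part of that is chance error at T1, which is not expected to recur at T2. A rise follows without any help from STEP 2.

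The other comparison on the page, STEP 1 only against STEP 1 plus STEP 2, misleads in the opposite direction: early responders are sorted into one group and non-responders into the other.

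**Working it through.** **Plan's own figure.** There is none to reproduce. The target of 50 rests on funding, resources and duration, and no SD or correlation is given.

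**Inputs from the article.** FACIT-F range 0-52; cut-off 34; 10-point gain; selection at T1. The two eligibility sentences overlap, so both readings are run:
- *Or* reading (the STEP 2 sentence as written): T1 < 34 or gain < 10.
- *And* reading (whoever is left after the no-STEP 2 sentence): T1 ≤ 34 and gain < 10.

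**Assumptions not in the article.** Baseline mean 28, SD 10, correlation r between occasions 0.7 to 0.9, uniform true STEP 1 gain 5, true STEP 2 effect 0. Clinical judgement and fast-tracking are not modelled.

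**Model.** Score at time t = mean at t + U + e_t, with Var(U) = 100r and Var(e_t) = 100(1 − r), clipped to 0-52. Means are 28 at T0 and 33 at T1 and T2. With independent errors, and apart from clipping, the expected T1-T2 change among those selected is −E(e at T1 | selected). This is positive whenever selection favours low T1.

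**Hand check, selection on level only.** For T1 < 34 with T1 mean 33 and SD 10, z = (34 − 33)/10 = 0.1 and φ(z)/Φ(z) = 0.397/0.540 = 0.735. The rise is (1 − r) × 10 × 0.735, which is 2.2 at r = 0.7 and 0.7 at r = 0.9. The simulated values for the two actual rules should lie either side of this.

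**Simulation, 1,000,000 people per scenario, STEP 2 group:**

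| Entry reading | Share entering | T1-T2, r = 0.7 | T1-T2, r = 0.9 |
|---|---|---|---|
| *Or* | 83-92% | +1.1 | +0.3 |
| *And* | 45-49% | +3.2 | +1.1 |

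At r = 0.7 under the *and* reading, T0-T1 is +0.6 and T0-T2 is +3.8, so 3.8 − 0.6 = 3.2. STEP 2 appears to supply most of the gain while doing nothing.

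**Is T0-T2 itself spurious?** No. Under the *and* reading it is +3.8 to +4.6 against a true STEP 1 gain of 5 put into the model. With no STEP 1 gain it is about 0 to −0.5.

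**Group contrast.** In a second scenario (SD 10, reliability 0.75, mean 30, STEP 1 gain 5 with SD 5, STEP 2 effect 0), T0-T2 is +11.9 for STEP 1 only against +3.1 for STEP 1 plus STEP 2 (*or*), and +7.2 against +1.7 (*and*). STEP 2 recipients look 11.9 − 3.1 = 8.8 or 7.2 − 1.7 = 5.5 points worse through selection alone. Because true STEP 1 gain varies here, the sorting acts on real response as well as on error. Across the scenarios tried, the gap ran from about 0 to 9.3.

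**Why subtraction is not enough.** In people with both assessments it gives the mean T1-T2 change but not its SD, which is √(s₁² + s₂² − 2ρs₁s₂). With both change SDs assumed to be 8, the result is 9.5, 8.0, 6.2 or 3.6 for ρ = 0.3, 0.5, 0.7 or 0.9. A paired figure has to be reported.

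**Would a fresh score at the start of STEP 2 cure it?** With exchangeable scores, restart-to-T2 returns 0.0. With correlation decaying over time (0.7-0.9 per 5 weeks; assumed times 0, 5, 6.5 and 10.5 weeks; *and* reading), T1-T2 is +0.8 to +2.5 and restart-to-T2 is +0.6 to +1.7. About 70% of the inflation remains (1.7/2.5 = 0.68; 0.6/0.8 = 0.75).

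**The case against.** The best defence is that the article never promises a STEP 2 increment. Its primary aim is feasibility, its secondary aim is the whole pathway, and it says it is not powered for effectiveness. For that aim T0 is the right reference. This stands, and it limits the point to how a secondary, descriptive outcome will be read.

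A reader might infer that the planned T0-T2 gain is false, or that the plan presents it as a STEP 2 benefit. The documents support neither. The analysis is labelled change from baseline in people who had both steps, and the gain in the calculation is STEP 1 gain that was put in.

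The inflation can also be called small. Under the *or* reading it is at most 1.1 points, against the 10 points the article treats as clinically important. If every eligible person starts STEP 2 and is assessed, there would be about 0.83 × 50 ≈ 42 starters at r = 0.7. With a T1-T2 SD of 7.2, the standard error is 7.2/√42 = 1.1, so the inflation is about one standard error. Under the *and* reading, with 0.45 × 50 ≈ 22 starters, it is 3.2/(7.2/√22) = 3.2/1.5, about two standard errors. Which applies depends on eligibility sentences that do not agree.

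Finally, T1 is the selecting score for FACIT-F only. PSEFSM and EQ-5D-5L are affected only as far as they correlate with it. That stands too.

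An extra descriptive line might be left to an unseen analysis plan. But the choice of T0 as the reference and the split by step are stated here, and together they invite the misreading.

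**Conclusion.** The point holds as a modest, low-cost improvement. The planned T0-referenced changes suit the pathway aim but do not describe the STEP 2 phase. For FACIT-F, the T1-T2 rise obtained by subtraction is inflated by roughly +0.3 to +1.1 points (*or* reading) or +1.1 to +3.2 (*and* reading) when STEP 2 has no effect. The group contrast is biased against STEP 2. These sizes rest on the assumed mean, SD, correlation and STEP 1 gain; the direction rests only on T1 being both the selecting score and the starting score.

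It would go too far to say that a restart score yields the STEP 2 effect. Even where regression to the mean is fully removed, a single-arm study cannot separate STEP 2 from time or other care. The primary feasibility aim is unaffected.

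**What to change.** 1. Keep T0-T2 as the whole-pathway figure.
2. For participants who start STEP 2, add the paired T1-T2 change (mean, SD, 95% CI). Label it uncontrolled and, for FACIT-F, inflated by selection on T1. Count separately any fast-tracked participants with no T1 score before STEP 2.
3. State that neither this change nor the STEP 1-only versus STEP 1 plus STEP 2 contrast estimates the effect of STEP 2.
4. Optionally, repeat the 13-item FACIT-F at the first STEP 2 session and report the paired change from that score to T2, called uncontrolled change during STEP 2. It reduces regression to the mean but does not always remove it.
5. Reconcile the two overlapping STEP 2 eligibility sentences, because they define the analysis groups. For example, a T1 score of 38 with a gain of 4 meets both.

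Items 1 to 3 use data already planned and cost one table line and one sentence. Item 4 adds one short form for STEP 2 starters only: about half the cohort under the *and* reading, but 83-92% under the *or* reading. The downside is slight respondent burden and probably a smaller figure for the STEP 2 phase.

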This paper describes a research protocol to investigate the feasibility of stepped-care CBT for individuals experiencing persistent CRF, entitled ‘REFRESH’ (ACTRN: ACTRN12622000420741). This is a single-arm exploratory study design. Standard Protocol Items: Recommendations for Interventional Trials (SPIRIT) guidelines were used to guide the reporting of the current feasibility study (see Fig. 1). The primary aim of the REFRESH study is to examine the acceptability, satisfaction, appropriateness and feasibility of an evidence-informed stepped-care CBT intervention for adults with persistent fatigue after cancer treatment. A secondary aim is to explore whether participation in the stepped-care intervention shows promise for improvements in fatigue, quality of life and self-efficacy.

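### Change scores and effect sizes for the secondary aim are planned by treatment path, with no interval and no whole-cohort estimate (minor)

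*Protocol article*

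**What the plan says.** The Background section of the protocol article sets the secondary aim: "A secondary aim is to explore whether participation in the stepped-care intervention shows promise for improvements in fatigue, quality of life and self-efficacy". It describes the design in one line: "This is a single-arm exploratory study design".

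Data analysis gives the sample size and its basis: "The target sample of 50 participants is based on available funding, resources (e.g. clinician time to deliver STEP 2) and study duration of 12 months". It then plans a rate with a Poisson 95% CI for recruitment, and proportions with Wilson 95% CIs for adherence and retention.

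For the three participant measures the plan is different. Changes from baseline "will be analysed descriptively (means and standard deviations". On grouping: "This will be done separately for participants who undertake STEP 1 only and for those who participate in STEP 1 and STEP 2". The effect size is "in this case, mean change divided by the baseline standard deviation". The section names no interval for the changes or the effect sizes, no estimate for all participants together, and no choice between a subgroup and a full-cohort baseline SD.

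The section on eligibility for STEP 2 bases the path on the T1 FACIT-F score and its change since T0, together with a psychologist's judgement.

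**The concern.** The effect sizes are the evidence on whether the program "shows promise for improvements in fatigue, quality of life and self-efficacy". They come from at most 50 people, and the plan divides those people in two. Reported without an interval, a moderate effect size looks equally solid whether it comes from 50 people or 15. The section already treats intervals as the normal way to report recruitment, adherence and retention, so their absence here is uneven.

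The split raises a second matter. The paths are not random halves of the cohort, because participants are sorted largely on the outcome being summarised. If only by-path results are reported, no estimate is free of that sorting, and adding intervals to the by-path results alone would not cure it.

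**Working it through.** **Inputs from the protocol article.** Target N = 50; effect size = mean change / baseline SD; FACIT-F important difference 10 points; STEP 1-only path if T1 FACIT-F is above 34 or has risen by at least 10 points. No SD of change, pre-post correlation, subgroup size or precision target is given, so there is no planned figure to reproduce.

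**Assumptions.** SD of FACIT-F change 8 to 12 points; pre-post correlation ρ = 0.5 (varied from 0.3 to 0.7); true effect size 0.5; n = 50, 25 and 15. With N = 50 the smaller path cannot exceed 25; 15 is only an illustration.

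**1. Mean change.** Half-width of the 95% CI = t(0.975, n−1) × SD / √n.

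| n | t | SD 8 | SD 10 | SD 12 |
|---|---|---|---|---|
| 50 | 2.010 | 2.3 | 2.8 | 3.4 |
| 25 | 2.064 | 3.3 | 4.1 | 5.0 |
| 15 | 2.145 | 4.4 | 5.5 | 6.7 |

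Example: 2.064 × 10 / √25 = 4.1 points. This needs only the SD of change and n, so a reader of the planned tables could compute it.

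**2. Effect size.** The 2.5th and 97.5th percentiles of mean change / baseline SD were simulated from bivariate normal samples (20,000 or more per setting). Repeat runs agree to within about 0.01 for ρ = 0.5 and 0.03 otherwise.

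| n | ρ = 0.3 | ρ = 0.5 | ρ = 0.7 |
|---|---|---|---|
| 50 | 0.17 to 0.87 | 0.22 to 0.83 | 0.28 to 0.77 |
| 25 | 0.05 to 1.06 | 0.11 to 0.99 | 0.20 to 0.90 |
| 15 | −0.12 to 1.29 | 0.00 to 1.18 | 0.11 to 1.06 |

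A hand check for ρ = 0.5 uses SE ≈ √[2(1−ρ)/n + ES²/(2(n−1))].

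- n = 50: √(0.0200 + 0.25/98) = √0.0226 = 0.150, so 0.5 ± 1.96 × 0.150 = 0.21 to 0.79.
- n = 25: √(0.0400 + 0.25/48) = √0.0452 = 0.213, so 0.08 to 0.92.

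The simulated ranges lie slightly higher because dividing by an estimated SD skews the ratio upward.

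**3. What sorting on the outcome does.** Assume no true change at all: T0 and T1 both with mean 28 and SD 10, ρ from 0.5 to 0.8, 50 participants, and everyone who meets the step-out rule counted as STEP 1 only. At T1, with the full-cohort baseline SD as denominator:

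- STEP 1-only group: mean effect size about 0.35 (ρ = 0.8) to 0.79 (ρ = 0.5).
- Its paired-t 95% CI lies wholly above zero in roughly 45% (ρ = 0.8) to 90% (ρ = 0.5) of runs.
- Whole cohort: the paired-t 95% CI lies wholly above zero in about 2.5% of runs, as it should.

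So a by-path interval can look convincing when nothing has changed. The whole-cohort interval is not distorted by this sorting.

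**The case against.** The strongest defence is that the plan does not offer bare point estimates. It commits to SDs, and with the SD of change and n the CI of each mean change follows by the formula in step 1. A reader might infer that improvement cannot be told from noise at all; for mean changes that is untrue. What remains is that the effect-size interval is less direct, and that readers would have to rebuild it themselves for three measures, two paths and two follow-ups.

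Descriptive analysis is also a legitimate choice for an exploratory single-arm study whose Discussion says that it is not powered for effectiveness, and a fuller plan that is not shown may add intervals. This stands as a reason for low severity. It does not dispose of the point: an interval describes precision and is not a test, and the article does name interval methods for other outcomes in the same section.

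Three stronger readings lack support in the document. Subgroup sizes are not given, so a figure such as 15 to 35 per path is a guess, and one path could hold most participants. The effect-size denominator is called only the baseline SD, so a subgroup SD is one reading and not a stated choice. Nothing says that these estimates will be used to plan an efficacy trial; the abstract's conclusion makes the assessment of feasibility the first step.

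**Conclusion.** The point holds as a minor reporting weakness. The effect sizes that serve the secondary aim are planned without intervals, by path, and with no whole-cohort estimate named. Their uncertainty is material even with all 50 participants: about 0.22 to 0.83 around an assumed true value of 0.5, widening to 0.11 to 0.99 at 25. These ranges rest on normal data, correlation 0.5 and unselected groups; correlations of 0.3 to 0.7 change the widths but not the conclusion.

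A reader might go on to infer that promise should be judged from an interval in each path. The document does not support that, because it sets the path by T1 FACIT-F and its change, so by-path intervals carry selection and regression to the mean. The size of that effect in step 3 depends on the assumed mean, SD and correlation, and on applying the rule mechanically without the psychologist's judgement. Nor does a whole-cohort interval show cause: without a control arm it measures sampling error only.

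**What to change.** Amend the change-score paragraph under Data analysis as follows.

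- For FACIT-F, PSEFSM and EQ-5D-5L, report whole-cohort mean change at T1 and T2 with a paired-t 95% CI, and the effect size with a bootstrap 95% CI that resamples participants.
- Base any statement of promise on these whole-cohort intervals. State beside the T2 result that T2 falls at 10 weeks for those who do STEP 1 only and at the end of STEP 2 for the others.
- Keep the by-path results with n and CIs, and use the full-cohort baseline SD as the common denominator so that both paths share one scale. Label them descriptive, with a note that the path depends on T1 FACIT-F and its change.

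The cost is a few lines of R and a few sentences, with no extra data and no design change. The downside is that the whole-cohort results will look less certain than bare effect sizes would.

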As a contingency, participants who are too distressed or unable to engage with the self-help program within two weeks after commencing STEP 1 can be fast tracked to STEP 2 (see below).

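### Change from baseline is summarised only within step groups formed mainly on T1 fatigue, with no whole-cohort summary to answer the program-level secondary aim

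*Protocol article*

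**What the plan says.** The secondary aim, in the Background, is about the program: "A secondary aim is to explore whether participation in the stepped-care intervention shows promise for improvements in fatigue, quality of life and self-efficacy".

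The Data analysis section sets the summary: "Changes from baseline at follow-up assessments for fatigue (FACIT-F), self-efficacy (PSEFSM) and quality of life (Ed-5D-5L) will be analysed descriptively (means and standard deviations"). It continues: "This will be done separately for participants who undertake STEP 1 only and for those who participate in STEP 1 and STEP 2". Effect sizes are "mean change divided by the baseline standard deviation"; whose baseline SD is meant is not said. No change summary across all participants is stated there or elsewhere in the article.

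Group membership is set under Eligibility for STEP 2: "Eligibility for STEP 2 is based on a participant’s change in fatigue scores following STEP 1". A T1 FACIT-F above 34, or a gain of at least 10 points, leads to no further CBT. A T1 score below 34, or a gain of less than 10, leads to consideration for STEP 2 together with the psychologist's judgement. A contingency also applies before T1: participants too distressed or "unable to engage with the self-help program within two weeks after commencing STEP 1 can be fast tracked to STEP 2".

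The last assessment is taken "At 10 weeks post T0 (for STEP 1 only completers) or at the completion of STEP 2".

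**The concern.** People stay in the STEP 1-only group largely because their T1 score was high or had risen by 10 points or more. The mean T0-T1 change in that group is then reported as its result. Ordinary visit-to-visit variation in FACIT-F is enough to make this mean positive, and it pushes the mean in the STEP 1 + STEP 2 group the other way. The effect is strongest for FACIT-F at T1, weaker at T2, and reaches PSEFSM and EQ-5D-5L only as far as they correlate with FACIT-F.

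The secondary aim asks about participation in the whole stepped-care program. Two means conditional on T1 fatigue do not answer that, and the one summary free of this sorting, change in everyone, is not planned. At stake is how the secondary results are read. No test or decision rule depends on them.

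**Working it through.** The article gives no SD, correlation or expected change for FACIT-F, so there is no figure of its own to reproduce. The check asks what the planned summaries would show if nothing changed.

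**Inputs from the article.** FACIT-F runs from 0 to 52 and higher is better; the cut-off is 34 and the clinically important difference 10 points; n = 50; the effect size is mean change divided by baseline SD.

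**Assumptions, not in the article.** Main set: mean 26 and SD 9 at T0, T1 and T2; correlation between visits 0.5 to 0.8; no true change; scores rounded and limited to 0-52. A participant is STEP 1 only if T1 > 34 or T1 - T0 >= 10, and everyone else takes STEP 2. Clinical judgement and fast-tracking are not modelled.

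**Results, main set (1,000,000 simulated participants per scenario)**

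| Summary | r = 0.8 | r = 0.5 |
|---|---|---|
| STEP 1 only, T0-T1 | +4.0 | +8.9 |
| Effect size, group's own baseline SD | 0.41 | 0.79 |
| STEP 1 only, T0-T2 | +0.9 | +2.8 |
| STEP 1 + STEP 2, T0-T1 | -1.0 | -3.1 |
| Whole cohort, T0-T1 | 0.0 | 0.0 |

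The effect size also depends on the denominator. In these runs the baseline SD was 9.8 (r = 0.8) and 11.3 (r = 0.5) in the STEP 1-only group, against 7.7 and 8.0 in the other group. With the assumed cohort SD of 9, the STEP 1-only values become 4.0/9 = 0.44 and 8.9/9 = 0.99.

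**Wider assumptions.** Over 18 sets (mean 22, 26 or 30; SD 8 or 10; correlation 0.5, 0.7 or 0.85) the STEP 1-only change ran from +1.7 to +11.6 at T1 and from +0.1 to +4.5 at T2. The STEP 1 + STEP 2 change at T1 ran from -0.3 to -4.4. The whole cohort stayed at 0.0.

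**Consistency check (mean 26, SD 10, r = 0.7).** 26.1% are STEP 1 only with +6.3 at T1, and 73.9% are STEP 1 + STEP 2 with -2.2. Pooled: 0.261 × 6.3 - 0.739 × 2.2 = 1.64 - 1.63, or about 0.

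**Trials of 50 (same set).** Over 4,000 simulated trials, the STEP 1-only T1 mean was above zero in 99.65%. The whole-cohort mean averaged 0.0, with 95% of trials between -2.1 and +2.2.

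**Incomplete uptake.** Suppose only 60% of those not released take STEP 2, at random, and the rest are counted as STEP 1 only. In the same set the STEP 1-only share is 0.261 + 0.4 × 0.739 = 0.557. Its T1 mean is (0.261 × 6.3 - 0.296 × 2.2)/0.557 = (1.64 - 0.65)/0.557, or about +1.8. With 80% uptake it is +3.2, and with 40% it is +0.9. In the main set (SD 9), 60% uptake gives about +0.9 to +2.5.

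**The case against.** The study is a feasibility study. The aim is secondary and exploratory, the analysis is descriptive, and the Discussion says the study is not powered for effectiveness. Reporting by step is natural in stepped care. Both groups are reported, so a reader can rebuild the pooled mean from group sizes and means. Table 2 also plans a whole-cohort measure, the proportion needing step 2, and the Discussion's remark on at least half of participants improving concerns everyone. Judgement, uptake and fast-tracking dilute the sorting. All of this stands, and it limits the weight of the point. It does not remove it: the pooled SD and effect size cannot be recovered directly from group means, a proportion is not a change estimate, and dilution leaves the STEP 1-only figure positive.

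It can also be said that an article condenses a fuller plan, which might contain a pooled summary. But the article does more than stay silent. It fixes how change is to be analysed, and fixes it by step.

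Several stronger readings are tempting but not supported:
- A T1-T2 rebound in the STEP 2 group would not be reported. Only change from baseline is planned, and there the sorting biases that group downwards.
- Fast-tracked participants cannot be said never to have done STEP 1; the text has them commencing it.
- Dividing by each group's own baseline SD is one possible reading, not a stated rule.
- Null effect sizes well above 2 arise only if release required both a high T1 score and a 10-point gain. The release sentence joins the two with 'or'.

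**Conclusion.** The point holds and should be fixed, but it does not undermine the study. As written, the by-step summaries of FACIT-F are shaped by the sorting rule, and nothing stated answers the program-level aim. With no true change, the STEP 1-only group would show about +4 to +9 points at T1 (effect size about 0.4 to 0.8 on its own baseline SD) and +1 to +3 at T2. The STEP 2 group would show about -1 to -3 at T1, and the whole cohort 0. These sizes rest on the assumed mean, SD and correlation, on the release sentence as modelled, and on full uptake of STEP 2. The groups are formed mainly, not solely, on T1 fatigue, and with 60% uptake the T1 figure is about +1 to +2.5.

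A reader might infer that the plan as a whole would declare STEP 1 effective when nothing changed. That goes too far: the other group is reported beside it with a change at or below zero on average, and the proportion needing STEP 2 is reported too.

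**What to change.** In Data analysis:
- Make T0-T1 and T0-T2 change in all participants with data, regardless of step, the lead summary for FACIT-F, PSEFSM and EQ-5D-5L, with 95% CIs.
- Name the whole-cohort baseline SD as the single effect-size denominator.
- Keep the by-step tables as secondary, and label them as groups selected on T1 fatigue.

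The two sentences under Eligibility for STEP 2 must be reconciled. A participant with T1 above 34 and a gain below 10, or with T1 below 34 and a gain of 10 or more, meets both, so group membership depends on the reading. Which rule should apply is for the investigators.

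The report should also say what the whole-cohort figure cannot do. It removes the sorting artefact, but not regression to the mean from screening on fatigue, nor natural recovery, because there is no control arm.

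The cost is some wording, a few table columns and a less favourable STEP 1 figure. No new data are needed.
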